**Exclusion criteria:**	
Have had endometriosis related surgery in the previous 6 months or have any surgery planned during the study period.	
Started or stopped/removed any hormonal contraceptive within the last 6 months. This includes the oral contraceptive pill (GnRH-a or danazol), implant contraceptives and the Mirena.	
Started, stopped or changed dosage on any pharmaceutical medication or herbal/natural medicine targeting endometriosis symptoms (such as pregabalin, Nortriptyline, or other Chinese herbal medicine) in the previous 6 months	
Having a known allergy or intolerance to any of the ingredients in Gynoclear™	
Participant has previously used Gynoclear™ for any condition.	
Participant is currently using a herbal supplement that contains any of the main constituents of the Gynoclear™ formula (e.g. Mediherb Endofem).	
Usage of anticoagulants (e.g. Warfarin, Heparin, Eliquis, Pradaxa, Xarelto) or any other medication, including nutritional and/or herbal supplements that may cause blood thinning (e.g. Vitamin E, *Gingko biloba*).	
History of coagulation disorders.	
Currently pregnant or breast feeding or planning on becoming pregnant during the study period.	

Based on a 20% difference in pain (measured by a 0–10 NRS) between groups (a moderate effect size *d* = 0.5 and a clinically significant difference), a standard deviation in pain scores of 2.2 (based on pilot data), an alpha of 0.05 and a power of 80% would mean 74 participants would need to be recruited. Given a predicted 20% drop out rate, 90 participants in total (45 per group) will be recruited. At the time of manuscript submission, 24 participants have been randomised.

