### Randomisation

After signing the informed consent document and satisfying the eligibility criteria, participants will be randomised in a 1:1 ratio to either the active treatment group (Gynoclear™) or the placebo control.

Using Castor EDC’s randomisation function, a randomisation sequence using a block size of 6, with 1:1 group allocation, was performed on the 15th of January 2019 by NICMs Clinical Trial Manager who is external to this study. Randomisation numbers were allocated in permuted blocks of 6 containing 3 active and 3 placebo randomisation numbers. The investigator will allocate each randomisation number in order of number sequence starting with the lowest number in each block and using all numbers in a block of 6 before starting with the lowest number in the next block of numbers. As soon as the randomisation number is assigned, it will be recorded on the participant log, in the patient notes and case report form. Details of any patients randomised out of sequence will be notified immediately to the Chief Investigator.

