#### Health-related quality of life questionnaires

The Endometriosis Health Profile-30 (EHP-30) is an endometriosis specific health-related quality of life measure [14]. It covers pain, control and powerlessness, social support, emotional well-being and self-image. These 30 questions provide the core of the EHP-30. The EHP also includes optional secondary modules that may not be appropriate to all participants. If participants are currently working, they will be asked to fill in the ‘Work’ module, if they are currently in a sexual relationship, they will be asked to fill in the ‘Sexual relationship’ module. All measures have a 1 month recall and will be taken twice online; at baseline and at the end of the 4-week follow-up period.

The EQ-5D [15] and SF12 [16] are validated health-related outcome measures and provide the necessary data for economic analysis and have been recently used in our economic analysis of the impact of endometriosis in Australia [17]. The EQ-5D is administered via Castor EDC and the SF-12 will be administered via paper-based methods due to cost, at baseline and at the end of the 4-week follow-up period.

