#### Fatigue severity scale (FSS)

The fatigue severity scale is a nine-item, seven-point questionnaire used to determine the impact of fatigue when performing daily activities [18]. This will be used as an adjunct to the numerical ratings given for daily fatigue, to provide a measure of the real-world impact of fatigue. This tool uses a seven-day recall. This will be administered online at baseline and at the end of the intervention.

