### Analysis plan

All data is captured via Castor EDC digitally, there are no paper instruments used in this trial. Data will be exported from Castor EDC into SPSS v24 (or greater). Prior to analysis, data will be cleaned by examining frequencies, means, medians, and ranges to identify logical errors. Instruments will be coded according to their respective scoring instructions. Unless specified by the instrument, missing items will be imputed based on averaging values within the instrument for a given individual, if no more than 15% of items are missing. Otherwise, that instrument will be set to missing for the individual.

Baseline demographics will be reported using descriptive statistics. Daily pain scores (as measured by the EPDD) will be converted into a single pain score at five time points, baseline, month 1, month 2, trial exit/end of intervention and follow-up. This single pain score will be achieved by taking the mean of the daily pain scores for the previous 4 weeks. Both a per-protocol and intention to treat analysis will be undertaken for the primary outcome of changes in pain scores. The same process of generating a single score will be used for the following outcomes: pain interference with activities of daily living (0–10), use of analgesics (number of days per month needing additional medication), severity of fatigue (0–10) and severity of dyspareunia (0–10). All scores will be analysed using repeated measures at baseline, month 1, month 2, trial exit and follow-up via a longitudinal linear mixed model analysis of variance with time and group as fixed effects and subject as a random effect.

Secondary outcomes of changes in EHP-30 scores, SF-12 scores and EQ-5D scores will be analysed using analysis of variance between baseline and one-month follow-up. FSS scores will be analysed using paired analysis of variance between baseline and the end of the intervention. Baseline values with be used as covariates in the analysis.

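### The Fatigue Severity Scale analysis is written as a paired before–after test with no active-versus-placebo contrast, and the matching sentence for EHP-30, SF-12 and EQ-5D is ambiguous

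*Protocol article*

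**What the plan says.** All the relevant sentences are in the Analysis plan of the protocol article.

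- **FSS:** "FSS scores will be analysed using paired analysis of variance between baseline and the end of the intervention".
- **EHP-30, SF-12 and EQ-5D:** changes in these scores "will be analysed using analysis of variance between baseline and one-month follow-up".
- **Covariate, directly after the FSS sentence:** "Baseline values with be used as covariates in the analysis".
- **Diary-derived scores, in the paragraph before:** a "longitudinal linear mixed model analysis of variance with time and group as fixed effects and subject as a random effect". This covers pain, activity interference, analgesic use, daily fatigue and dyspareunia.

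On measurement times, the FSS section says "This will be administered online at baseline and at the end of the intervention", and Table 4 agrees. The EHP-30 is "taken twice online; at baseline and at the end of the 4-week follow-up period". Each instrument therefore yields one baseline and one later value per woman.

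On design, the Randomisation section says "participants will be randomised in a 1:1 ratio to either the active treatment group (Gynoclear™) or the placebo control".

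**The concern.** In a placebo-controlled trial the question for each outcome is whether the arms differ. The FSS sentence instead names a within-person comparison of two occasions and gives no role to treatment group. The next sentence adds a covariate that is already one of the two paired values. An analyst cannot follow both sentences literally and must choose between a test of change over time and a comparison of active with placebo.

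The choice matters because some improvement in both arms is plausible. Placebo response is one source, since the Discussion notes that all outcome measures are self-reported. Regression to the mean is another. Women enter on a four-week mean diary pain of at least 4/10, and that same diary serves as baseline. Entry does not select on FSS, so regression to the mean can reach it only through its correlation with pain.

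**Working it through.** **1. Which contrast each sentence names**

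| Outcome | Stated method | Contrast named | Group named? |
|---|---|---|---|
| Diary-derived scores | Linear mixed model | Time and group | Yes |
| EHP-30, SF-12, EQ-5D | ANOVA of changes, baseline as covariate | Baseline vs one-month follow-up | No |
| FSS | Paired ANOVA, baseline as covariate | Baseline vs end of intervention | No |

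One consequence is that the secondary objective on fatigue in Table 3 would be tested with a group term for the daily diary score and, as written, without one for FSS.

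**2. When the covariate conflicts with the paired test**

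Let B be baseline, F the later score and G the randomised group. A paired ANOVA on two occasions tests whether the mean of F − B is zero. There B is half of the response, and no coefficient describes active versus placebo.

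If group is added, the conflict goes. The model F − B = a + tG + bB rearranges to F = a + tG + (1 + b)B, so the treatment coefficient t is that of ordinary ANCOVA. The conflict therefore holds for the FSS sentence as written, and not for every repeated-measures model that contains group.

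**3. Size if the paired test is run in the active arm**

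The plan gives no figure to reproduce on this point. Inputs:

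- Arm size: 74/2 = 37, from the 74 participants in the sample-size paragraph after Table 1. Whether 74 is itself right is a separate matter.
- True treatment effect: zero.
- Improvement common to both arms: 0, 0.3 or 0.5 SD (assumed).
- Baseline/follow-up correlation r: 0.3, 0.5 or 0.7 (assumed).
- Nominal level 0.05; 4,000 simulated trials per setting.

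With unit variances the SD of change is √(2(1 − r)). The expected paired t statistic is roughly √37 × shift / √(2(1 − r)). For a 0.3 SD shift:

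- r = 0.3: 6.083 × 0.3/1.183 = 1.54
- r = 0.5: 6.083 × 0.3/1.000 = 1.82
- r = 0.7: 6.083 × 0.3/0.775 = 2.36

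Simulated rejection rates:

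| Common shift | r | Paired test, active arm | Between-arm ANCOVA |
|---|---|---|---|
| 0 | 0.3 / 0.5 / 0.7 | 5.0% / 5.2% / 5.6% | 4.7% / 4.8% / 5.5% |
| 0.3 SD | 0.3 / 0.5 / 0.7 | 32% / 43% / 64% | 4.3% / 4.7% / 4.7% |
| 0.5 SD | 0.3 / 0.5 / 0.7 | 71% / 83% / 97% | 4.6% / 4.8% / 5.6% |

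The simulation error at 5% is √(0.05 × 0.95/4000) = 0.34 percentage points, so the ANCOVA column is consistent with 5% throughout. ANCOVA on change gave the same rejection rates as ANCOVA on the later score.

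**The case against.** The strongest reply is that these are condensed sentences in a journal article. The Data sharing plan says a full protocol exists, and a group term is the kind of detail it would hold. In a two-arm trial an ANOVA of changes needs a grouping factor, and arm is the obvious one. With baseline as covariate, that is ANCOVA on change. On this reading the covariate sentence shows that a between-arm analysis was intended and that the word paired was loose. The cost-effectiveness paragraph also commits EQ-5D to a difference between arms, though only for the economic analysis.

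For EHP-30, SF-12 and EQ-5D much of this stands. The reading is fair, and those outcomes should be called ambiguous rather than wrong. It does not rescue FSS. There the article does not merely omit a detail: it names a paired test and the two occasions it compares. The paragraph before also shows that group is written down when the diary model is described.

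Two further objections stand as limits on size. The document gives neither the shift nor the correlation. And no section says that a within-arm change will be used to claim efficacy.

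**Conclusion.** The FSS analysis is wrong as written. It specifies a within-person test of change, names no active-versus-placebo contrast, and conflicts with its own covariate sentence. The sentence for EHP-30, SF-12 and EQ-5D needs clarifying.

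Under a 0.3 SD improvement common to both arms and no treatment effect, a paired test in the active arm would reject in roughly 32–64% of trials, against about 5% for between-arm ANCOVA. This rests on the assumed shift, on correlations of 0.3 to 0.7, and on the test being run in the active arm alone. With no common shift the paired test also rejects in about 5%.

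A reader might infer three stronger claims, which the document does not support:

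- **That all secondary outcomes lack a treatment comparison.** The diary-derived ones use a model that names group.
- **That baseline can never be a covariate in such a model.** It can, once group is included.
- **That a test pooling both arms shows the size of the error.** Its rejection rates are higher (58–91% at a 0.3 SD shift), but no section proposes a pooled test as evidence of efficacy.

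**What to change.** Delete the word paired and replace the two sentences on these instruments and the covariate sentence with: *FSS (end of intervention) and EHP-30, SF-12 and EQ-5D (one-month follow-up) will each be analysed by ANCOVA of the post-baseline score on randomised group, with the baseline score as covariate. The adjusted between-group difference and its 95% confidence interval will be reported. Within-arm changes are descriptive only.*

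If ANCOVA was intended all along, this only makes it explicit. The cost is analysis-plan wording: no visit, questionnaire or sample size changes. It should be settled before the data are unblinded.

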### Data monitoring and stopping guidelines

Data will be monitored by [name] and MA for completeness, plausibility and consistency to ensure the integrity and completeness of the data set. Any queries will be resolved by the Chief Investigator or delegated member of the study team. Adverse events will be regularly monitored via the online daily diary, as well as at each study visit conducted over the phone by the research team. Any serious adverse events will trigger an alert to the Chief Investigator and reporting to relevant authorities as per the National Health and Medical Research Council guidelines.

### Study timeline

The expected duration of the data collection phase of this study will be 12 months, with 14 time points where data is collected. The schedule of enrolment, interventions and assessments as per SPIRIT [20] is outlined in Table 4.

**Table 4 Tab4:** Timeline of treatment assessments and interventions

Procedure	Screening (week 0)	Baseline (week 4)	Phone call (week 6)	Midpoint (week 10)	End of treatment (week 16)	Post-treatment follow-up (week 20)
Informed consent	X					
Inclusion and exclusion	X					
Medical history	X					
Screening blood test: LFT and U&E		X				
Randomisation		X				
Treatment/placebo dispensed		X				
End of treatment blood test: LFT and U&E					X	
Concomitant medication collection		X	X	X	X	X
Participants electronically fill out Endometriosis Pain Daily Diary v3 Scores	X	X	X	X	X	X
Quality of life forms (SF-12, EQ-5D, EHP-30)		X				X
Fatigue severity scale (FSS)		X			X	
Participant expectation and satisfaction questionnaire		X			X	
Adverse events			X	X	X	X
Dispense/return study drug		X		X	X	

### Dissemination of findings

A lay summary of the findings will be provided to all relevant endometriosis support and advocacy groups in Australia and via articles through organisations such as The Conversation. Dissemination through the academy will be via peer-reviewed publications in appropriate journals and at scientific conferences.

### Data sharing plan

After the completion of the study, data will be made available to researchers upon review and approval of the submitted protocols by the research team. The full trial protocol is available via the principal investigator.

## Discussion

Herbal medicine is very commonly recommended by natural health practitioners in Australia and New Zealand, including naturopaths [21] and Chinese medicine practitioners [22], to treat the symptoms of endometriosis. Gui Zhi Fu Ling Wan is the most common Traditional Chinese herbal medicine prescription used in the treatment of endometriosis [23] and includes ingredients commonly recommended by naturopaths and western herbalists [24]. However, the evidence of effectiveness for herbal medicine is limited. Systematic reviews of studies investigating Chinese herbal medicine for endometriosis have been inconclusive due to a lack of high-quality trials [25] and a previous study using raw herbs made into a decoction had issues with finding an inert placebo [26]. While many practitioners use variable complex herbal formulations as part of their treatment protocols [27], the convenience of an encapsulated ‘off-the-shelf’ formula, that can be dispensed through pharmacy and herbal medicine dispensaries may increase the availability of herbal medicine to women with endometriosis.

The economic burden of endometriosis is similar to or higher than other chronic disease burdens such as heart disease and diabetes [28]. Our team has recently completed a study on the cost of illness burden of endometriosis in Australia and found that the total cost per woman per year is $31,137AUD [17]. Our research also examined the cost per woman based on their reported pain score and found that each reduction in pain scores by 20% reduced costs by a minimum of $9000 per woman per year. Therefore, effective pain management strategies are vital to reduce the economic disease burden and improve quality of life. Given that Australian women are already seeking out non-pharmacological treatment for endometriosis [9, 21], if Gynoclear™ is found to be an effective treatment to help reduce endometriosis-related pelvic pain and other associated symptoms of endometriosis, this could be an effective adjunct treatment for the more than 720,000 women with endometriosis in Australia.

Potential limitation to the trial that must be acknowledged is that all outcome measures are self-reported. This is due to the lack of reliable, non-invasive objective outcome measures currently available to track the progression or response to treatment [29]. However, these self-reported measures are in line with the recently developed core outcome set developed by a team of international experts, which do not currently recommend any objective outcome measures unless tracking fertility [30]. Other potential limitations are COVID-19 related, where the requirement for safety blood tests may impact some women’s decision to participate, potentially due to concerns about infection or limitations on travel due to lockdown or social distancing measures.

## Trial status

Protocol Version and Date: v6 23 Oct 2019

Date Recruitment Commenced: 01 Jun 2019

Expected Date of Completion: 31 Jul 2021

## Data Availability

Not applicable.

## Abbreviations

EPDD: Endometriosis Pain Daily Diary
EHP-30: Endometriosis Health Profile
SF-12: Short Form Health Survey
CPP: Chronic pelvic pain
GZFLW: Gui Zhi Fu Ling Wan
TCM: Traditional Chinese medicine
FSS: Fatigue severity scale
U&E: Urea and electrolytes
LFT: Liver function tests
AUD: Australian dollars
